#### Mechanical ventilation time

3.2.2

Data will be obtained to determine whether the mechanical ventilation time in ICU is shortened during the period from admission to the end of the trial.

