### Sample size

2.4

According to the preliminary clinical research data, the total effective rate of “improved sitting Wuqinxi” in preventing and treating common complications and adverse outcomes in mechanically ventilated patients was statistically different between the groups. The test level was α = 0.05. The test efficiency was 1 - β = 0.80. The sample size was estimated using G∗Power (version 3.1.2, Franz faul, Universitat kiwl, Germany), and the effect size was set as d = 0.50. After calculation, the number of participants needed in each group was 64, totaling to 128 participants. Considering an attrition rate of ≤20%, the total number of participants required for this study was calculated to be 160, with 80 participants in each group.

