#### Exclusion criteria

2.7.2

The following patients will be excluded:

(1)Patients with rapidly progressive neuromuscular diseases(2)Patients with Acute Physiology and Chronic Health Evaluation II score >30 and expected to die within 48 hours(3)Patients with increased intracranial pressure, limb disability or loss, and unstable fracture(4)Patients included in other clinical trials

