#### Length of ICU stay

3.2.3

The period from admission to discharge from the ICU will be recorded.

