#### Cost of hospitalization

3.2.4

Hospitalization expenses from admission to discharge from the ICU will be recorded.

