### Statistical analysis

3.7

Before analysis, the data of 2 participants with complete data will be carefully checked to ensure the accuracy of the data. All data will be analyzed by intention. SPSS version 22.0 (Chicago, IL) will be used to analyze the data. The measurement data will be represented as mean ± standard deviation. The paired t-test will be used to perform the before and after analyses of the same group. The chi-square test will be used for the counting data and the rank sum test will be used for grade data. The Kaplan–Meier method will be used for univariate analysis to explore each possible related factor. The multivariate Cox model will be used to adjust for variables with statistical significance (*P* < .05) in univariate analysis to detect the influence of these variables on the study measure outcomes.

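### Ventilation time, ICU stay and complications are defined without regard to death, so an arm with more early deaths could look better; mortality is not a listed outcome

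*Protocol article*

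**What the plan says.** Section 3.2 (Observation index) lists four outcomes.

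- **Complications (3.2.1):** impaired consciousness and delirium, ICU-acquired weakness, ventilator-associated pneumonia, pulmonary infarction and pressure ulcers, observed as simple incidence.
- **Ventilation time (3.2.2):** data are collected to "determine whether the mechanical ventilation time in ICU is shortened".
- **ICU stay (3.2.3):** "The period from admission to discharge from the ICU will be recorded".
- **Cost (3.2.4):** "Hospitalization expenses from admission to discharge from the ICU will be recorded".

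Lower is better on all four. None is defined as an event reached alive, none is combined with death, and death is not a fifth item.

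Section 3.7 summarises measurements as mean and standard deviation and states that "The chi-square test will be used for the counting data". It adds a rank sum test for graded data, and Kaplan–Meier and Cox models for exploring and adjusting for related factors. It defines neither event nor censoring for these models, and it names no method for competing events.

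On eligibility, Table 3 spans mild to severe ARDS and Section 2.7.1 sets no severity limit. The prognosis-based exclusion in Section 2.7.2 applies to patients with an APACHE II "score >30 and expected to die within 48 hours". As worded, both conditions must be met.

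Section 2.8 removes patients with incomplete data, whereas Section 3.7 commits to analysing all data by intention.

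**The concern.** Death ends ventilation and the ICU stay, and it ends the time during which a complication can be observed. An outcome that counts only days or only complications therefore gives an early death the same value as a fast recovery. If the arms differ in early mortality, part of the difference in ventilation time, stay and complications reflects who died rather than who recovered. This matters most where the intervention could do harm, because a harm acting through early death could be read as efficacy. Without mortality beside these outcomes, a reader of the results could not tell the two apart.

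**Working it through.** **1. The plan's own figure.** Section 2.4 gives "The test level was α = 0.05", "The test efficiency was 1 - β = 0.80" and "the effect size was set as d = 0.50". A two-sided two-sample t-test with these inputs needs 63.77, so 64 per group, or 128 in all; 128 / (1 − 0.20) = 160. The stated size reproduces (two-sided testing is inferred, not stated). No mortality rate enters it, so the article offers no figure from which to size the present problem. Everything below uses assumed mortality.

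**2. Simplest illustration.** Mean ventilation time = m × (days if died) + (1 − m) × (days if survived), where m is mortality. Survivors are assumed identical in both arms at 10 days.

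| Deaths occur at | m = 25% | m = 35% | Favours |
|---|---|---|---|
| 5 days | 0.25×5 + 0.75×10 = 8.75 | 0.35×5 + 0.65×10 = 8.25 | arm with more deaths |
| 12 days | 0.25×12 + 0.75×10 = 10.50 | 0.35×12 + 0.65×10 = 10.70 | arm with fewer deaths |

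The sign depends on whether deaths come before or after the time at which survivors are weaned.

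**3. Competing-risk model, no true benefit.** Assumed constant hazards, the same in both arms: weaning 0.10 per day (mean 10 days), complication 0.05 per day while ventilated, and a mean of 3 days from weaning to ICU discharge. Only the death hazard differs: 0.0137 per day in control and 0.033 in the experimental arm.

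- Mean ventilation time = 1 / (weaning + death hazard): 1/0.1137 = 8.8 days against 1/0.133 = 7.5 days.
- Complication incidence = 0.05 / (0.05 + 0.10 + death hazard): 0.05/0.1637 = 30.5% against 0.05/0.183 = 27.3%.
- ICU deaths = 1 − [0.10/(0.10 + death hazard)] × [(1/3)/(1/3 + death hazard)]: 15.5% against 31.6%.
- Mean ICU stay = ICU deaths / death hazard: 0.1552/0.0137 = 11.3 days against 0.3158/0.033 = 9.6 days.

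A simulation of the same model agrees (30.6% for control complications is sampling error). With 80 patients per arm and 2,000 simulated trials per row, against control deaths of 15.5%:

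| Experimental deaths | Ventilation (days) | ICU stay (days) | Complications | Trials with nominally significant shorter stay |
|---|---|---|---|---|
| 15.5% | 8.8 | 11.3 | 30.5% | 3% |
| 22.3% | 8.3 | 10.6 | 29.3% | 8% |
| 31.6% | 7.5 | 9.6 | 27.3% | 23% |
| 42.5% | 6.6 | 8.3 | 24.8% | 60% |

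The last column uses a rank test, which is an assumption: Section 3.7 does not say which test compares durations between arms. Cost was not simulated.

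**4. A measure that penalises death.** At 15.5% against 31.6% deaths, 28-day ventilator-free days with death scored as zero are 16.5 against 14.1. The comparison now points against the arm with more deaths.

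**5. Dropping the patients who die.** In step 2 this would give 10 against 10 days, but only because survivors were assumed identical. In step 3 it does not help: survivors' ventilation time is 8.8 against 7.5 days and their ICU stay 11.7 against 10.2 days, because slow weaners are more likely to die before weaning and so leave the survivor group.

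**The case against.** **The article is condensed.** Censoring rules and competing-event methods often sit in a full protocol or analysis plan, neither of which is shown. That stands for the methods. It does not cover the outcome definitions, which Section 3.2 does give and which measure total days or crude incidence irrespective of survival.

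**Deaths are not invisible.** Safety is a stated aim, Section 3.5 records the time and result of every adverse event whatever its cause, and serious events are reported within 24 hours. A reader might infer that the trial would conceal deaths; the article does not support that. What is absent from it is mortality among the outcomes, and even this rests on Section 3.2, since the abstract and Figure 2 are not shown.

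**The patients are selected.** A reader might picture an unstable cohort. Section 2.7.1 requires patients to be conscious, able to follow instructions and stable in heart and lung function, which may lower mortality. Deaths remain to be expected, but their rate is unknown.

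**No rule scores the dead as complication-free.** This is true. It is the default result of a crude incidence, it arises only when death precedes any complication, and complications before death still count.

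**Cox with deaths censored is legitimate.** Also true: it estimates the cause-specific hazard. The difficulty is with one minus the Kaplan–Meier curve, which treats the dead as if they could still be weaned.

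**Conclusion.** The point holds as a flaw in the stated outcome definitions: early death can pass for benefit on ventilation time, ICU stay and complications, and mortality is not listed beside them to expose it.

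It is tempting to go further and say that the arm with more deaths will look better on every outcome. The article does not support that. The direction holds when deaths come early relative to weaning and reverses when they come late (10.5 against 10.7 days in the second case above). Lower cost is plausible but uncertain, because daily cost near death may be higher.

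The size is wholly conditional. It is half a day in the simplest case with a ten-point mortality difference. In the constant-hazard model, a rise in deaths from 15.5% to 22.3% gives a spurious significant gain in ICU stay in 8% of trials, and a rise to 31.6%, about double, in 23%, against 3% with equal mortality.

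Excluding patients who die under the incomplete-data clause of Section 2.8 is no safe way out. It need not remove the bias, and it conflicts with the commitment in Section 3.7 to analysis by intention.

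**What to change.** 1. Redefine ventilation time as time to liberation from the ventilator alive, and ICU stay as time to ICU discharge alive, each with death as a competing event. Show cumulative incidence by arm in place of one minus Kaplan–Meier, and keep the Cox model as a cause-specific hazard model.
2. Report complications with death as a competing event, or as complication or death.
3. Report ICU mortality by arm beside these outcomes and beside cost.
4. State that patients who die stay in the analysis and are not treated as incomplete data, so that Sections 2.8 and 3.7 agree.

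The cost is mainly wording. Death and its date should already be in the ICU record and the adverse event form, and no follow-up after discharge is needed. The stated sample size of 160 contains no mortality input, so this point by itself does not change it. The downside is a slightly less simple summary than a mean in days.

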#### Length of ICU stay

3.2.3

The period from admission to discharge from the ICU will be recorded.

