### Randomization and allocation concealment

2.5

Members of the Sichuan Traditional Chinese Medicine Evidence-Based Medicine center will use SAS 9.2 software (SAS, Cary, NC) to generate 160 random serial numbers. After screening and baseline evaluation, mechanically ventilated ICU patients will be randomly divided into the experimental and control groups in a 1:1 ratio. The group allocation number will be provided in a continuously numbered sealed envelope of carbon-free paper. The envelope will be kept by the research administrator, who will not be directly involved in the recruitment or follow-up of any participants, and their group allocation number will be disclosed later. The administrator will open the envelopes and provide participants with their group allocation number on the day of inclusion. The distribution of patients in each experimental center is shown in Table 1.

**Table 1 T1:** Distribution of patients in each trial center.

Number of each center	Name of each center	Experimental group (patients)	Control group (patients)
01	Affiliated Hospital of Chengdu University of traditional Chinese Medicine	40	40
02	Leshan Hospital of traditional Chinese Medicine	20	20
03	Affiliated Hospital of Chengdu University	20	20
Total		80	80

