#### Inclusion criteria

2.7.1

Only patients who meet the following criteria will be included:

(1)Age ≥18 years.(2)Fulfillment of the diagnostic criteria of acute exacerbation of chronic obstructive pulmonary disease, acute respiratory distress syndrome, or postoperative respiratory failure requiring mechanical ventilation for ≥24 hours.(3)Clear consciousness and the ability to act in accordance with instructions.(4)Stable cardiopulmonary functions.(5)Voluntarily participation after signing an informed consent.

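### Ventilation time, ICU stay and cost are counted from admission rather than from randomisation, which leaves the expected absolute difference unbiased but shrinks relative effects and usually costs precision

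*Protocol article*

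**What the plan says.** Sections 3.2.2 to 3.2.4 of the protocol article fix the starting point of three outcomes:

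- Ventilation time (3.2.2): data are gathered to determine "whether the mechanical ventilation time in ICU is shortened during the period from admission to the end of the trial".
- ICU stay (3.2.3): "The period from admission to discharge from the ICU will be recorded".
- Cost (3.2.4): "Hospitalization expenses from admission to discharge from the ICU will be recorded".

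None of these sections says whether admission means admission to hospital or to the ICU.

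Allocation comes later. Section 2.5 states: "After screening and baseline evaluation, mechanically ventilated ICU patients will be randomly divided". Section 2.7.1 admits patients with a qualifying respiratory diagnosis "requiring mechanical ventilation for ≥24 hours". It also asks for "Clear consciousness and the ability to act in accordance with instructions", stable heart and lung function, and signed consent. Section 2.5 has the envelope opened on the day of inclusion, so the allocation date is known for every patient.

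Nowhere does the article start these outcomes at randomisation, subtract what came before it, or commit to adjusting for it.

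**The concern.** A randomised comparison should measure what happens after allocation. A patient must be in the ICU, ventilated, awake, cooperative and stable before entering, so some time always passes between admission and randomisation. The intervention cannot alter the ventilator days, ICU days or expenses of that interval, but the definitions add them to the outcome.

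Two things are at stake. First, any effect expressed as a ratio or percentage is drawn towards no difference, because the same untouched amount is added to both arms. Second, if the interval varies between patients, its variance is usually added to the outcome's variance, so the same absolute effect is harder to detect. The trial was sized on a standardised effect, which is the scale that shrinks.

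A related question concerns section 3.2.1. It does not say in so many words that a complication already present at the baseline evaluation is left out of the incidence counts.

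**Working it through.** **Reproducing the plan's own figure.** Inputs from section 2.4: α = 0.05, power 0.80, d = 0.50. Sidedness is not stated. A two-sided two-sample t-test needs 63.77, so 64 per group and 128 in total, as the article says. A one-sided test would need 51 and does not match. Allowing for 20% attrition, 128 / 0.80 = 160. The sample-size arithmetic is not in dispute.

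**Effect on the absolute difference.** Write the outcome from admission as A + B, with A the amount before randomisation and B the amount after. Randomisation gives A the same distribution in both arms, so the expected difference in A + B equals the expected difference in B. A simulation agrees. It used 64 per group, gamma-distributed B with means 8 and 6 days, and 3,000 replicates per setting. The mean difference was about 2.0 days with either starting point.

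**Effect on a ratio.** Assume a true 25% cut in 6 post-randomisation days, so B averages 6 against 4.5 (ratio 0.75). Adding the same number of earlier days to both arms gives:

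- 1 day: (1 + 4.5) / (1 + 6) = 0.786
- 2 days: (2 + 4.5) / (2 + 6) = 0.812
- 3 days: (3 + 4.5) / (3 + 6) = 0.833

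The absolute difference stays at 1.5 days throughout.

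**Effect on power.** Let k = SD(A) / SD(B) and ρ = the correlation of A and B. Neither is in the documents, so both are assumptions. Suppose also that d = 0.50 describes the effect on B. Then

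d′ = 0.50 / √(1 + k² + 2ρk)

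For example, k = 0.5 and ρ = 0 give 0.50 / √1.25 = 0.447. With 64 per group and two-sided α = 0.05:

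| k | d′ at ρ = 0 | Power at ρ = 0 | Power at ρ = 0.3 | Power at ρ = −0.25 |
|---|---|---|---|---|
| 0 (constant delay) | 0.500 | 0.801 | 0.801 | 0.801 |
| 0.25 | 0.485 | 0.777 | 0.722 | 0.826 |
| 0.5 | 0.447 | 0.709 | 0.616 | 0.801 |
| 0.75 | 0.400 | 0.612 | 0.507 | 0.731 |
| 1.0 | 0.354 | 0.510 | 0.413 | 0.630 |

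The loss depends on the spread of the delay and on its correlation with later time, not on its average length. At ρ = −0.25 there is none up to k = 0.5.

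**Time-to-event methods.** Section 3.7 names Kaplan–Meier and Cox without an event or a time origin. If they were applied to these durations from admission, each patient would be counted as at risk during time in which the event could not yet have been observed, since randomisation requires the patient to be still ventilated in the ICU. A delay common to all patients would leave the order of event times, and so the comparison, unchanged. Varying delays would not.

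**The case against.** The strongest reply is that this is not bias. Randomisation balances the earlier period in expectation, the absolute difference is preserved, and the test's error rate already covers chance imbalance. All of that stands.

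Several stronger readings are tempting, and the documents do not support them:

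- **That the trial's real power is nearer 0.51.** This needs a pre-randomisation spread as large as the later spread, and no SD is given. Section 2.4 introduces d = 0.50 through an overall effective rate for complications and adverse outcomes. It does not tie that value to ventilation days, ICU days or cost.
- **That every patient has spent at least 24 hours on the ventilator before entry.** The criterion can equally mean an expected need. That a delay exists follows from the other entry steps; its length and spread are unknown.
- **That the survival analyses are distorted.** Section 3.7 does not say which outcome they apply to, so this is conditional.
- **That complications present at entry will be counted.** Incidence ordinarily means new cases, a baseline evaluation exists, and its schedule (Figure 2) is not shown.

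It can also be said that sections 3.2.3 and 3.2.4 speak only of recording, that total stay and total cost are legitimate descriptions, and that an analysis plan could derive post-randomisation values from the known inclusion date. This is fair, but it does not remove the point. Section 3.2.2 ties the period from admission to the question of whether ventilation is shortened, which is the treatment comparison itself. The starting point is a stated definition, not a detail left open, and an analysis plan that followed it would carry it forward.

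**Conclusion.** The point holds as a weakness of definition and precision. Three outcomes include time or expense that precedes randomisation and cannot respond to treatment. The expected absolute difference is unaffected, relative effects are pulled towards no difference, and variance usually rises.

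If d = 0.50 applied to post-randomisation time and the two periods were uncorrelated, power at 64 per group would be about 0.78 to 0.51 for SD ratios of 0.25 to 1.0, against 0.80 with the clock started at randomisation. Positive correlation makes the loss larger. A near-constant delay or a modest negative correlation makes it small or absent. These are ranges under assumption, not a corrected power or sample size. If admission means hospital admission, the unaffected period is longer, most clearly for cost and for postoperative patients.

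A reader might infer a biased treatment comparison or a demonstrably underpowered trial. The documents show neither.

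**What to change.** - In sections 3.2.2 to 3.2.4, define the comparative outcomes from randomisation: ventilation time, ICU stay to ICU discharge, and expenses to ICU discharge.
- Keep totals from admission as descriptive figures only, and say whether admission means hospital or ICU.
- Prespecify ventilation days or ICU days before randomisation as a baseline covariate, included whatever its univariate P value. The P < .05 screen in section 3.7 does not guarantee that.
- If Kaplan–Meier or Cox is used for these durations, state randomisation as the time origin.
- In section 3.2.1, state that a complication already present at the baseline evaluation does not count as incident.

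The cost is a few lines of wording, since the inclusion date is already known. The one practical burden is that each bill must be split at the randomisation date.

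### Ventilation time, ICU stay and cost are counted from admission, not from randomisation, so they include time and expense that Wuqinxi cannot change; the precision lost runs from none to substantial, depending on a spread the protocol does not give

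*Protocol article*

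**What the plan says.** Three of the four observation indices in section 3.2 of the protocol article take admission as their starting point:

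- Ventilation time (3.2.2): the question is whether it "is shortened during the period from admission to the end of the trial".
- ICU stay (3.2.3): "The period from admission to discharge from the ICU will be recorded".
- Cost (3.2.4): "Hospitalization expenses from admission to discharge from the ICU will be recorded".

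Randomisation is placed later. Section 2.5 says "After screening and baseline evaluation, mechanically ventilated ICU patients will be randomly divided". Under the inclusion criteria (2.7.1), patients must have a qualifying condition "requiring mechanical ventilation for ≥24 hours", be clearly conscious, be able to follow instructions and have stable cardiopulmonary function. Section 2.5 also has the allocation envelope opened on the day of inclusion, so that date is known for every patient.

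Section 3.7 plans Kaplan–Meier for univariate exploration and a multivariate Cox model. It does not say which outcome is the event time, or what time zero is.

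**The concern.** Each of these outcomes is the sum of two parts: what accrued between admission and randomisation, which the intervention cannot touch, and what accrued afterwards, which it can. Randomisation balances the first part between arms only on average. Its patient-to-patient variation stays in the outcome as noise.

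Some variation is plausible from the eligibility rules alone. The trial mixes acute exacerbations of COPD, ARDS and postoperative respiratory failure, and each patient has to become awake and stable before entry. Shorter ventilation is also one of the benefits the introduction puts forward for Wuqinxi. A less precise estimate, or an understated percentage reduction, would therefore fall on a result that readers will look for.

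**Working it through.** **1. The plan's own figure.** Section 2.4 gives "The test level was α = 0.05", "The test efficiency was 1 - β = 0.80" and "the effect size was set as d = 0.50". The normal approximation is n = 2(1.96 + 0.842)²/0.50² = 62.8, so 63 per group. The exact noncentral-t calculation, two-sided, gives 64 per group (power 0.801; 0.795 at 63). With 20% attrition, 128/0.8 = 160. The stated figures reproduce.

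**2. Effect of the admission clock on a comparison of means.** Write outcome = pre + post, split at randomisation. Let r = SD(pre)/SD(post) and let ρ be the correlation of the two parts. The expected pre part is the same in both arms, so the absolute difference is unchanged. Only the SD changes:

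d′ = 0.50 / √(1 + r² + 2ρr)

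The inputs r and ρ are not in the protocol, so a range is assumed. Applying d = 0.50 to post-randomisation time is also an assumption. For ρ = 0:

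- r = 0.25: 0.50/√1.0625 = 0.485
- r = 0.5: 0.50/√1.25 = 0.447
- r = 1: 0.50/√2 = 0.354

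Two-sided t-test power at 64 per arm:

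| r | ρ = 0 | ρ = 0.3 | ρ = 0.5 |
|---|---|---|---|
| 0 (constant delay, or clock from randomisation) | 80.1% | 80.1% | 80.1% |
| 0.1 | 79.8% | 77.4% | 75.9% |
| 0.25 | 77.7% | 72.2% | 68.8% |
| 0.5 | 70.9% | 61.6% | 56.4% |
| 1 | 51.0% | 41.3% | 36.7% |

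On the normal approximation with ρ = 0, holding 80% power would need about 67, 79 and 126 per group at r = 0.25, 0.5 and 1, against 63 at r = 0.

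**3. Check with skewed stays.** This simulation used 64 per arm and a lognormal post-randomisation stay with an assumed control mean of 8 days and coefficient of variation 0.8. Constant delays of 1, 3 or 5 days left the t-test (70.7%), rank-sum (77.1%) and log-rank (72.4%) power unchanged. A delay of mean 2, SD 1 days cost about 1 to 3 points. A delay of mean 4, SD 4 days cost about 19 to 24 points.

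**4. Percentage effects.** These shrink even with a constant delay. As an illustration, a 1.6-day reduction on 8 post-randomisation days is 1.6/8 = 20%. With 4 earlier days counted in, it is 1.6/12 = 13%.

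**5. If Cox is applied to these durations on an admission clock.** Assume a hazard ratio of 1.65 from randomisation, a control mean of 6 days and 64 per arm. Simulation on the randomisation clock gives a hazard ratio of about 1.66 and 79% power. With pre-randomisation mean/SD of 3/2, 5/4 and 7/6 days, the estimated ratio falls to about 1.6, 1.5 and 1.4, and power to about 72%, 57% and 42%. A constant 5-day delay changes neither: the partial likelihood uses only the order of events, and an equal shift keeps that order.

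**The case against.** The strongest reply is that nothing here is shown to be large. A reader might infer that counting from admission costs a large part of the trial's power. The protocol does not support that. Days before randomisation cost nothing in themselves on the absolute scale; only their spread does, and no spread is given. If ρ is negative the loss is smaller, and at ρ = −r/2 it vanishes. Nor is any stated power lost: section 2.4 introduces the calculation with a total effective rate for complications and adverse outcomes, not with a duration or a cost. This stands.

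A reader might also infer that the Cox hazard ratio must be pulled toward 1. That holds only for a delay that varies between patients, and only if the model is fitted to these durations on an admission clock, which section 3.7 does not say.

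A third tempting reading is that chance imbalance in waiting time could pass for a treatment effect. With 80 per arm, SE = SD × √(2/80). The probability that the arms differ by at least 1 day before randomisation is about 21% if the SD is 5 days, 3.5% if it is 3 and 0.2% if it is 2. That variation is already in the standard error and does not raise the type I error.

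Two smaller replies also stand. The 24-hour criterion may mean expected need rather than ventilation already received, and a limit on time before entry may appear in the schedule figure or the full protocol. Whole-stay duration and cost are also meaningful quantities in their own right.

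None of this removes the core point. The starting point is written into three outcome definitions, and on either reading of the 24-hour criterion patients are ventilated, awake and stable when randomised. The Cox adjustment in section 3.7 is no reliable remedy: it keeps only variables significant in univariate analysis and does not name time before randomisation.

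**Conclusion.** The point holds as one of precision and interpretation, not of validity. All three outcomes include pre-randomisation time or expense. The comparison is not biased and the expected absolute difference is intact, but percentage effects are understated and variable waiting time adds noise.

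At 64 per arm with uncorrelated parts, the loss is nil for a constant delay, about 2 points at r = 0.25, 9 at r = 0.5 and 29 at r = 1. Positive correlation makes it worse, up to about 43 points at r = 1 and ρ = 0.5. These figures rest on a two-sided test, on d = 0.50 applying to post-randomisation time, and on assumed values of r and ρ. The case for changing the clock does not depend on where in that range the trial falls, because counting from randomisation removes the issue throughout it. The change is worth making but is not critical.

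**What to change.** - In 3.2.2, 3.2.3 and 3.2.4, define the between-arm outcome as ventilation time, ICU stay and cost accrued from randomisation.
- In 3.7, state that any Kaplan–Meier or Cox analysis of these durations uses randomisation as time zero.
- Keep the admission-based totals as descriptive results.
- Optionally, adjust each outcome for the matching amount accrued before randomisation as a prespecified baseline covariate, whatever its univariate significance.

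For ventilation time and ICU stay this is a change of wording, since the inclusion date is already known and the admission date is needed in any case. For cost, expenses must be split at the inclusion date, which needs dated billing. If that is not available, keep total cost as defined and say in the report that it includes expense from before randomisation.
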